### Compliance

We will perform indirect (pill count) and direct (AED blood levels) methods to check for compliance to AED treatment. We will train community volunteers to assist the research team and local health team with the follow-up of the trial participants and for compliance monitoring at the home of the participants. The center visit at week 2 is scheduled to check for side effects in order to minimize withdrawal from AED treatment. Although noncompliant patients are expected to be equally distributed among treatment arms because of randomization and therefore not influence outcome, it is important to put effort into minimizing noncompliance, especially since we intend to continue treatment with AEDs past the duration of the trial regardless of the results. Community volunteers will also be trained to become community directed distributors of ivermectin after completion of the trial.

### Endpoints

Primary endpoint is proportion of patients who have achieved seizure freedom after 4 months. Seizure freedom will be defined as no seizures the last month of the trial (month 4). Secondary endpoints are proportion of patients at month 4 with more than 50% reduction in seizure frequency compared to reported seizure frequency at randomization and microfilarial load measured in skin snip. The seizure frequency data will be collected starting from day 1 using a seizure diary. Reduction of seizures will be compared between ivermectin and nonivermectin arms.

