**Objective:**

The goal of the study is to assess whether ivermectin treatment decreases the frequency of seizures and leads to seizure freedom in OAE patients, including patients with NS. If we are able to demonstrate such an effect, this would strengthen the argument that onchocerciasis is causing epilepsy and therefore we should increase our efforts to eliminate onchocerciasis.

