**Methods:**

We will conduct a randomized clinical trial in the Democratic Republic of Congo to compare seizure freedom in onchocerciasis-infested epilepsy patients who receive immediate ivermectin treatment with delayed (after 4 months) ivermectin treatment. All participants will simultaneously receive antiepilepsy drugs (AEDs) according to local guidelines for epilepsy treatment. The primary endpoint is seizure freedom defined as no seizures during the 4 month of follow-up. Secondary endpoint is significant (>50%) seizure reduction compared to baseline seizure frequency. Reduction of seizures will be compared between ivermectin and nonivermectin arms.

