### Sample Size Calculation

We expect that 4 months of treatment with AEDs (phenobarbital, carbamazepine, or sodium valproate) will lead to seizure freedom in 50% of the patients (experience of [name] in Uganda). In a clinical trial performed in Rethy (Ituri) comparing the safety and parasitological efficacy of moxidectin versus ivermectin treatment in persons with *O volvulus* infection not receiving antiepileptic treatment, 6 (80%) of 7 trial participants with epilepsy were seizure free at 4 months.

Null hypothesis: The probability of seizure freedom at 4 months for immediate ivermectin treatment is equal to the probability of seizure freedom at 4 months for delayed ivermectin treatment. If we expect that seizure freedom at 4 months will be obtained in 50% of the participants with phenobarbital alone and that with additional ivermectin treatment 80% of patients will achieve seizure freedom at 4 months, about 104 subjects (52 per group) are needed to achieve the power of 90% to reject the null hypothesis at the 5% significance level. Considering that 5% of the patients will be lost to follow-up, 110 patients will be enrolled in the trial.

All comparative analyses will be based on the intention-to-treat principle: all randomized patients will be included in the analysis according to the result of the randomization.

For the primary endpoint, the null hypothesis will be tested by comparing the observed proportion of responses in arm A with the corresponding proportion in arm B at the 1-sided 5% significance level by using the Cochran-Mantel-Haenszel test for comparison of 2 independent proportions. The Cochran-Mantel-Haenszel test will be performed controlling for baseline frequency of seizures. The same test will be used for the secondary endpoint. Change versus baseline in skin micofilarial load at month 4 will be analyzed by means of a *t* test. Frequencies of seizures will be compared between participants with and without positive microfilaria skin snips at month 4.

Patients lost to follow-up will be regarded as nonresponders. Similarly, patients for whom the AED regimen had to be adapted because of an increasing number of seizures will be considered as nonresponders. AED treatment changes because of side effects or possible interactions with other drugs will not be considered as treatment failure.

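### One seizure-free month counts as seizure freedom in patients who may enter at 2 seizures per month, so a positive primary result would not by itself show that ivermectin leads to seizure freedom

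*Protocol article*

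**What the plan says.** Under Endpoints, the primary endpoint is the proportion seizure free after 4 months, and the operative rule is: "Seizure freedom will be defined as no seizures the last month of the trial (month 4". The Methods paragraph of the abstract gives another window: "The primary endpoint is seizure freedom defined as no seizures during the 4 month of follow-up".

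The selection criteria (Diagnosis of Epilepsy) set an entry floor of 2 seizures per month and no upper limit. Both arms receive antiepileptic drugs. The objective in the abstract is to "assess whether ivermectin treatment decreases the frequency of seizures and leads to seizure freedom in OAE patients".

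For the control arm, the Sample Size Calculation assumes that "seizure freedom at 4 months will be obtained in 50% of the participants with phenobarbital alone". For the ivermectin arm the planning value is 80%. The section concludes that "about 104 subjects (52 per group) are needed to achieve the power of 90% to reject the null hypothesis at the 5% significance level". It does not say whether these rates refer to month 4 alone or to all four months. The primary test is planned "at the 1-sided 5% significance level by using the Cochran-Mantel-Haenszel test", controlling for baseline seizure frequency. Patients lost to follow-up, and those whose drug regimen is changed because seizures increase, count as nonresponders. The seizure diary runs from day 1.

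**The concern.** At the entry floor the mean gap between seizures is half a month, so the window used to certify freedom is only two mean gaps long. Residual rates below 2 per month are to be expected because all patients start antiepileptic drugs, and empty months are then more common still. Patients with active epilepsy can therefore be counted as seizure free.

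What is at stake is the conclusion. The protocol treats fewer seizures and seizure freedom as different claims: the objective names both, and a reduction of more than 50% is a separate secondary endpoint. Under the month-4 rule, the primary endpoint cannot tell the two apart.

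**Working it through.** **1. The plan's own figure.** Inputs from the Sample Size Calculation: 50% and 80%, 90% power, 5% level. With pooled variance and a two-sided test, n per arm = [1.960·√(2·0.65·0.35) + 1.282·√(0.25 + 0.16)]² / 0.30² = 51.0, rounded up to 52, or 104 in total. Then 104/0.95 = 109.5, rounded up to 110. The stated size reproduces. Powers below use 52 per arm and the planned one-sided 5% test: power = Φ{[d − 1.645·√(2p̄(1−p̄)/52)] / √[(p₁(1−p₁) + p₂(1−p₂))/52]}. For 50% vs 80% this is 95.0%.

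**2. Chance of an empty window.** Assumption, not in the documents: Poisson seizures at a constant rate r per month, so P(no seizure in t months) = exp(−r·t).

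| Rate per month | Month 4 only | Months 3–4 | All 4 months |
|---|---|---|---|
| 4 | 1.8% | 0.03% | <0.01% |
| 2 (entry floor) | 13.5% | 1.8% | 0.03% |
| 1 (floor halved) | 36.8% | 13.5% | 1.8% |

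If rates vary between patients (gamma, dispersion φ from 0.5 to 2, same mean r), P = (1 + φ·r·t)^(−1/φ). At a mean of 2 per month this gives 25% to 45% for one month and 4% to 24% for four. At a mean of 1 it gives 44% to 58% and 11% to 33%. Some patients then lie below the mean rate, so these figures illustrate sensitivity and do not describe patients exactly at the floor.

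**3. Could the planned rates arise with nobody seizure free?** Under Poisson timing, an empty-month rate of 50% needs −ln 0.5 = 0.69 seizures per month, and 80% needs −ln 0.8 = 0.22. Over four months 0.5⁴ = 6% and 0.8⁴ = 41% would remain free of seizures. The planned month-4 result is thus compatible with a pure rate reduction.

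**4. Effect on the arm difference.** Two models give different answers.

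*A truly seizure-free subgroup.* Suppose a share s is truly free and the rest have the same chance c of an empty month in both arms. The observed rate is s + (1−s)c and the difference is 0.30·(1−c). With s = 50% and 80%:

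| c | Observed rates | Difference | Power |
|---|---|---|---|
| 0 | 50.0% vs 80.0% | 30 points | 95% |
| 13.5% | 56.8% vs 82.7% | 26 points | 90% |
| 36.8% | 68.4% vs 87.4% | 19 points | 76% |

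*A pure rate reduction (Poisson, ratio 0.5).*

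| Control rate per month | Month 4 only | All 4 months |
|---|---|---|
| 2 | 13.5% vs 36.8% (23 points) | 0.03% vs 1.8% (2 points) |
| 0.5 | 60.7% vs 77.9% (17 points) | 13.5% vs 36.8% (23 points) |

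From a high control rate the one-month window separates the arms better, and from a low one the longer window does. The direction is not fixed.

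**The case against.** The strongest reply is that this is a short proof-of-concept trial with an openly stated endpoint, whose objective also includes fewer seizures. A month-4 difference supports that half of the objective, and the secondary endpoint on reduction covers it too. The entry criterion is a floor, no baseline distribution is given, and at 4 per month a chance gap is rare. Treating drug changes for increasing seizures as nonresponse removes some false responders. Under the abstract's four-month definition the problem nearly vanishes with Poisson timing.

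Much of this stands, and it limits the point to what may be concluded. It does not remove it. Controlling for baseline frequency balances the comparison but reclassifies nobody. The nonresponder rule leaves untouched a patient with occasional, non-increasing seizures. The abstract's definition helps only if it is the one adopted.

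A reader might infer that the endpoint dilutes the treatment effect and leaves the trial underpowered. The documents do not support that. Dilution needs a truly free subgroup and equal chance gaps in both arms, and it can reverse under a rate reduction. If 50% and 80% are already month-4 rates, chance responders are included in them and planned power is unaffected.

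A reader might also infer that months 3–4 should replace month 4 as primary. That is debatable. It would add a third window to two that already conflict, and it would begin right after the 2-month visit, at which drug doses may be raised. It is not proof of freedom either: at 0.69 and 0.22 seizures per month, 0.5² = 25% and 0.8² = 64% would have both months empty with nobody seizure free.

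**Conclusion.** The point holds as a limit on interpretation. Under the month-4 rule, a material share of patients near the entry threshold, or at drug-reduced rates, would count as seizure free by chance: about 13.5% at 2 per month and 37% at 1 per month, against 1.8% at 4 per month. These figures rest on Poisson timing, and variation between patients raises the first two. A significant primary result would show fewer patients with seizures in month 4 and would not by itself establish that ivermectin leads to seizure freedom.

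Dilution is conditional. If 50% and 80% were true sustained rates with equal chance gaps, the 30-point difference would fall to between 26 and 19 points, with one-sided power of about 90% to 76%. A loss of power cannot be shown from the protocol, because the window behind the planning rates is not stated.

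**What to change.** Reconcile the abstract and the Endpoints section to one primary definition, and state in the Sample Size Calculation which window the 50% and 80% refer to.

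If month 4 stays primary:

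- Name it *no seizures in month 4*.
- Add two named secondary endpoints from the day-1 diary, each with the same Cochran-Mantel-Haenszel test: *no seizures in months 3–4*, and *no seizures over the 4 months of follow-up* (the abstract's definition).
- Say that ivermectin leads to seizure freedom only if the longer-window estimates favour ivermectin, and report the window length with the claim. Otherwise conclude only on seizures in month 4.

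The cost is revised wording and one or two more tables, with no new visits, data or patients. The longer-window rates will be lower than 50% and 80% if those are month-4 rates. If the four-month definition becomes primary instead, the planning rates must be justified for that window.

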### Baseline and Follow-Up Procedures

At baseline, information will be collected on seizure semiology, frequency, risk factors, treatment history, and ivermectin treatment in the past. A full physical and neurological examination will be performed together with serological testing and skin snip examination. Weight and height measurements will be carried out and the participant body mass index will be calculated at baseline and follow-up visits. Trial participants will be instructed on how to fill out a seizure calendar and record intake of AEDs. A center visit is scheduled 2 weeks after randomization to assess potential side effects of AEDs. Side effects will be recorded using a structured questionnaire inquiring about known side effects of phenobarbital, carbamazepine, or sodium valproate. To assess seizure frequency, center visits are scheduled after 2 weeks, 1, 2, 3, and 4 months. To minimize loss to follow-up, we use Global Positioning System coordinates to locate study participants. During these visits, neurological and physical examination will be repeated, adverse events will be evaluated, and we will count AED pills for indirect measurement of AED compliance. At the fourth visit, skin snip examination and *O volvulus* serology will be repeated. Additionally, AED blood levels will be measured to directly assess AED compliance (Table 1).

**Table 1 table1:** Overview of study baseline and follow-up assessments.

Overview procedures	Trial stage						
	t=–1	t=0	t=2w	t=m1	t=m2	t=m3	t=m4
Check of inclusion and exclusion criteria	X						
Patient characteristics questionnaire	X						
Physical exam and neurological assesment	X		X		X	X	X
Seizure diary review	X		X	X	X	X	X
Administering AED^a^/ivermectin		X	X	X	X	X	X
AED pill count	X		X	X	X	X	X
Blood exam, skin snip, urine test	X						X
Adverse event questionnaire		X	X	X	X	X	X

^a^AED: antiepilepsy drug.

If a participant is not able to visit the study center, a home visit will be performed to monitor AED use and seizure frequency.

### Sample Size Calculation

We expect that 4 months of treatment with AEDs (phenobarbital, carbamazepine, or sodium valproate) will lead to seizure freedom in 50% of the patients (experience of [name] in Uganda). In a clinical trial performed in Rethy (Ituri) comparing the safety and parasitological efficacy of moxidectin versus ivermectin treatment in persons with *O volvulus* infection not receiving antiepileptic treatment, 6 (80%) of 7 trial participants with epilepsy were seizure free at 4 months.

Null hypothesis: The probability of seizure freedom at 4 months for immediate ivermectin treatment is equal to the probability of seizure freedom at 4 months for delayed ivermectin treatment. If we expect that seizure freedom at 4 months will be obtained in 50% of the participants with phenobarbital alone and that with additional ivermectin treatment 80% of patients will achieve seizure freedom at 4 months, about 104 subjects (52 per group) are needed to achieve the power of 90% to reject the null hypothesis at the 5% significance level. Considering that 5% of the patients will be lost to follow-up, 110 patients will be enrolled in the trial.

All comparative analyses will be based on the intention-to-treat principle: all randomized patients will be included in the analysis according to the result of the randomization.

For the primary endpoint, the null hypothesis will be tested by comparing the observed proportion of responses in arm A with the corresponding proportion in arm B at the 1-sided 5% significance level by using the Cochran-Mantel-Haenszel test for comparison of 2 independent proportions. The Cochran-Mantel-Haenszel test will be performed controlling for baseline frequency of seizures. The same test will be used for the secondary endpoint. Change versus baseline in skin micofilarial load at month 4 will be analyzed by means of a *t* test. Frequencies of seizures will be compared between participants with and without positive microfilaria skin snips at month 4.

Patients lost to follow-up will be regarded as nonresponders. Similarly, patients for whom the AED regimen had to be adapted because of an increasing number of seizures will be considered as nonresponders. AED treatment changes because of side effects or possible interactions with other drugs will not be considered as treatment failure.

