## Methods

### Study Design

This is a proof-of-concept randomized treatment trial consisting of 2 treatment arms, immediate (arm A) and delayed (4 months later) ivermectin treatment (arm B). A computer-based, preplanned age and frequency of seizures stratified randomization list will be used. The trial will not be placebo-controlled as this will be costly and we do not expect this to greatly influence reporting of seizures, our primary outcome. Epilepsy patients in both arms will additionally receive antiepileptic drugs (AEDs) following local guidelines of epilepsy treatment in DRC. Study investigators collecting and analyzing data will be blinded for treatment.

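### Randomisation is stratified by age and seizure frequency, but the Cochran-Mantel-Haenszel test controls for seizure frequency only: still valid, but mildly conservative if age predicts seizure freedom

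*Protocol article*

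**What the plan says.** Under Study Design, the protocol article describes the allocation: "A computer-based, preplanned age and frequency of seizures stratified randomization list will be used". Two factors therefore define the strata.

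Under Sample Size Calculation, the primary endpoint is tested "at the 1-sided 5% significance level by using the Cochran-Mantel-Haenszel test for comparison of 2 independent proportions". The control variable follows: "The Cochran-Mantel-Haenszel test will be performed controlling for baseline frequency of seizures". The article then assigns the same test to the secondary endpoint. Given the list under Endpoints, this means the more than 50% reduction in seizure frequency, because microfilarial load has its own t test.

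The article gives no reason for leaving age out of the test. It gives no figure for the effect of age on seizure freedom, and its sample size calculation does not mention stratification.

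**The concern.** Stratified allocation balances the arms on age, so age contributes little to the chance difference between them. A test that ignores age still counts age-related variation in its variance. If age is related to outcome, that variance is too large for the design and the p value is slightly too big. The stake is a little power, and a primary analysis that does not match the randomisation.

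An age effect is plausible. Entry is from 5 years with no upper limit, and the carbamazepine and valproate regimens differ between adults and children. Choosing age as a stratum also suggests that it was thought relevant.

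This is not a detail left to an unseen analysis plan, because the article itself names the test and its control variable.

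**Working it through.** **1. The plan's own figure.** Inputs from Sample Size Calculation: "seizure freedom at 4 months will be obtained in 50% of the participants with phenobarbital alone", "with additional ivermectin treatment 80% of patients will achieve seizure freedom at 4 months", and a sample size chosen "to achieve the power of 90% to reject the null hypothesis at the 5% significance level". With pooled variance and no continuity correction, the number per arm is

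n = [z(α)·√(2·p̄·(1−p̄)) + z(0.90)·√(p0(1−p0) + p1(1−p1))]² / (p1−p0)²

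with p0 = 0.5, p1 = 0.8 and p̄ = 0.65.

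- Two-sided 5%: (1.960 × 0.6745 + 1.282 × 0.6403)² / 0.09 = 51.01, rounded up to 52 per arm, or 104. Power at 52 per arm is 90.6%.
- 1-sided 5%: the same formula with 1.645 gives 42 per arm. Power at 52 per arm is 95.0%.
- Loss to follow-up: 104 / 0.95 = 109.5, so 110.

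The stated 104 and 110 reproduce as an unstratified two-sided calculation, so the planned power does not rely on adjustment for age. The difference in sidedness from the stated test is a separate matter. Results are given both ways below.

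**2. Why the test becomes conservative.** Take the null hypothesis with 50% seizure freedom, two equal age groups and an age odds ratio of 5. For simplicity, ignore seizure frequency.

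- Group rates: √5/(1+√5) = 0.691 and 0.309.
- Variance per patient within age groups: 0.691 × 0.309 = 0.2135. Ignoring age: 0.25.
- Ratio 0.2135/0.25 = 0.854, with square root 0.924.
- The nominal critical value 1.645 acts like 1.645/0.924 = 1.780, a true 1-sided error of about 3.8%.

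At an odds ratio of 3 the same steps give rates of 0.634 and 0.366, a variance of 0.232, a square-root ratio of 0.963, and a true error of about 4.4%. At an odds ratio of 1 nothing changes.

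**3. Simulation.** The Cochran-Mantel-Haenszel statistic is

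z = Σ(a_k − n_1k·m_1k/n_k) / √Σ[n_1k·n_0k·m_1k·m_0k / (n_k²(n_k−1))]

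where, in stratum k, a_k is the number of responders in arm A, n_1k and n_0k are the arm sizes, and m_1k and m_0k are the numbers with and without response. It was computed with strata by frequency only and by age × frequency.

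- From the article: 104 patients, 1:1 allocation, overall rates of 50% and 80% (50% in both arms for type I error).
- Assumed: two frequency levels with outcome odds ratio 2, two equal age levels, permuted blocks of 4, 20,000 trials per setting.

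Each cell shows frequency only / age × frequency. Two-sided power is the proportion with z > 1.96 in favour of ivermectin.

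| Age odds ratio | Type I error, 1-sided 5% | Power, 1-sided 5% | Power, two-sided 5% |
|---|---|---|---|
| 1 | 4.9% / 5.0% | 95.5% / 95.5% | 91.3% / 91.3% |
| 2 | 4.4% / 4.7% | 95.7% / 95.8% | 92.0% / 92.3% |
| 3 | 4.4% / 5.2% | 95.9% / 96.3% | 91.9% / 92.6% |
| 5 | 3.5% / 5.0% | 96.0% / 96.9% | 92.3% / 93.9% |

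The simulation standard error of a 5% rate is √(0.05 × 0.95/20,000) = 0.15 points.

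With three age levels the gain from including age was at most 0.6 points 1-sided and 1.1 points two-sided. At odds ratio 5 the 1-sided type I error without age was 4.2%.

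A separate run with 110 patients, 2 × 2 strata and the same overall rates, at 1-sided 5%, gave:

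- Odds ratio 2.7: type I error 4.6% / 5.0%, power 96.7% / 97.0%.
- Odds ratio 5: type I error 3.9% / 5.1%, power 96.9% / 97.7%.

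It showed no cost to including age at odds ratio 1.

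**The case against.** The case for leaving the plan alone is that nothing in the article shows age to be prognostic for seizure freedom. Its statements on age concern the onset and incidence of epilepsy, not response to treatment, and onset is restricted to 5 to 18 years. If age has no effect, nothing is lost. The error is in the safe direction, and 52 per arm already gives about 95% power at the stated 1-sided level. Prespecifying adjustment for one of two stratification factors, plausibly the one closest to the outcome, is defensible. All of this stands and limits the size of the point, but the mismatch with the design remains.

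A reader might infer more than the documents support, in three ways.

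- **That power is certainly lost.** The loss depends on an age effect that the documents do not give.
- **That power falls well below 90%.** Fixing the treatment log odds ratio at 1.386 and the age odds ratio at about 7.4 gives, two-sided, about 82% power without age and 87% with it. But under that model the overall rates shrink to about 50% and 75%, so most of the apparent shortfall from 90% is a smaller treatment effect than planned. Even the test that includes age reaches only 87%. The same model at the stated 1-sided level gives 89.3% and 92.7%. Nothing in the article supports an odds ratio of that size.
- **That a reported confidence interval is too wide.** The article specifies no interval and no risk difference for these endpoints.

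**Conclusion.** The inconsistency is real and minor. The plan randomises within two factors and tests within one, for the primary endpoint and for the more than 50% reduction endpoint. Type I error is not inflated. For assumed age odds ratios of 1 to 5, the omission costs about 0 to 1 point of power at 1-sided 5%, and up to about 1.5 points two-sided. The 1-sided type I error falls to about 3.5% to 4% at the top of that range. Power stayed above 90% in every setting with the rates held at 50% and 80%.

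The direction follows from the design. The size rests on assumed age and frequency effects, numbers of levels and block size, and on the planned rates being met. If 5% are lost in each arm and counted as failures, the rates become 47.5% and 76%. Unstratified power with 55 per arm is then 93.3% 1-sided and 87.8% two-sided, whatever is done about age.

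**What to change.** State that the Cochran-Mantel-Haenszel test for seizure freedom and for the more than 50% reduction endpoint is stratified by both randomisation factors, using the age and seizure-frequency categories of the randomisation list. If age is to stay out, give the reason. Settle this before unblinding, so that there is no later choice between two p values.

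The cost is one phrase in the analysis text. Age is already known for every patient, and no new data are needed. The small downside is sparser strata: with 104 patients, four equal cells hold 104/4 = 26 each and six hold about 104/6 = 17, and a cell with patients from only one arm contributes nothing to the test. In the simulations this cost nothing material, even when age had no effect.
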